## Abstract

**Background::**

Chronic prostatitis/chronic pelvic pain syndrome (CP/CPPS) is a common urinary system disease in men. As part of traditional Traditional Chinese medicine, acupuncture has been widely used in clinical practice. In order to evaluate the exact effect of acupuncture on the clinical efficacy of CP/CPPS, this experiment uses randomized controlled experiments.

**Methods/design::**

This pragmatic randomized controlled trial will recruit 166 patients who are diagnosed with CP/CPPS. Simple randomization to conventional drug treatment with a 1:1 allocation ratio will be used. Ten 30-minute acupuncture sessions will be provided to patients assigned to the Intervention group. All participants will continue to receive conventional drug treatment. The selection of outcomes will be evaluated by Health's Symptom Score Index (NIH-CPSI) score at week 4.

**Discussion::**

This trial may provide evidence regarding the clinical effectiveness, safety, and cost-effectiveness of acupuncture for patients with CP/CPPS.

**Trial registration::**

ClinicalTrials.gov, ChiCTR1900021132, Registered on 29 January 2019

## Introduction

1

Chronic prostatitis/chronic pelvic pain syndrome (CP/CPPS) is a common urinary system disease in men.^[1,2]^ The main symptoms of CP/CPPS include recurrent, long-term pelvic floor area, lumbosacral pain and discomfort, and varying degrees of lower urinary tract symptoms (frequency, urgency, dysuria, endless urination, etc.). Some patients also experience dizziness, fatigue, memory loss, sexual dysfunction, and even depression.^[3,4]^ Epidemiological surveys show that 2.2% to 13.8% of adult men worldwide are affected by this, while 30% to 50% of men are affected at some time in their lives.^[5]^ Related literature reports that the prevalence of CP/CPPS and related symptoms in China is as high as 46.6%. CP/CPPS not only causes great pain to the patient's body and mind, but also causes severe social burden due to its multiple and repetitive nature.^[6]^ In view of this, the National Institutes of Health (NIH) has currently listed CP with myocardial infarction, unstable angina pectoris, and active Crohn disease as the most serious chronic diseases that affect residents’ quality of life.^[7,8]^

As part of traditional Traditional Chinese medicine (TCM), acupuncture has been widely used in clinical practice. Recent studies have shown that acupuncture is effective in reducing chronic pain and anti-fibrosis in the pelvic floor area. Studies have shown that acupuncture stimulates the patient's analgesic system by stimulating related acupoints, accelerates the production of endogenous opioid peptides in the central nervous system and acts on the corresponding receptors, thereby achieving the effect of peripheral analgesia.^[9,10]^ Anti-inflammatory effects can also be achieved by increasing β-Ep levels in inflammatory tissues and serum.^[11,12]^ TCM believes that acupuncture can adjust the balance of Qi and blood in the human body, and stimulates acupuncture points to improve human function. It is more and more popular with doctors and patients for its unique advantages of simplicity, convenience and effectiveness.

In order to evaluate the exact effect of acupuncture on the clinical efficacy of CP/CPPS, this experiment uses randomized controlled experiments. We will verify the clinical efficacy of acupuncture treatment for CP/CPPS by observing the effects of acupuncture combined with tamsulosin hydrochloride sustained-release capsules on the improvement of symptoms and mental health in patients with CP/CPPS.

## Methods/design

2

### Study design and settings

2.1

A brief flowchart of the entire study is shown in Figure 1. We will perform a 2-group, randomized, single-blind, placebo-controlled, multi-center trial that will evaluate the efficacy and safety of acupuncture for patients with CP/CPPS. This study will use a completely random grouping and parallel control observation design method. We will ensure the balance of the baseline data of the two groups through a sufficient sample size and a completely randomized grouping method. This study will be approved by the Ethics Committee of Dongzhimen Hospital Affiliated to Beijing University of Chinese Medicine. We will not begin recruiting at other centers in the trial until local ethical approval has been obtained. This study is registered at http://www.chictr.org.cn/showproj.aspx?proj=35685 (ChiCTR1900021132).The protocol includes elements recommended in the Standard Protocol Items: Recommendations for Interventional Trials checklist (Additional file 1).

**Figure 1 F1:**
[figure not shown]
Study design flow chart.

### Setting and participants

2.2

This study will be conducted in China. Patients will be recruited from Urology/Andrology departments of Dongzhimen Hospital. We will enroll participants based on the following inclusion criteria:

1.Those who meet the CP / CPPS western medical diagnostic criteria;2.Those whose disease course exceeds 3 months;3.Twenty years old ≤ age ≤ 50 years old;4.Patients who have been treated before the consultation can be included in the study after at least 2 weeks of drug withdrawal;5.Those who have signed informed consent.

Participants who meet the following exclusion criteria will not be enrolled:

1.Patient with a history of pelvic surgery;2.Persons with abnormal development or infection of urogenital system;3.Prostate tuberculosis, benign prostatic hyperplasia and prostate cancer, acute urethral syndrome;4.Patients with severe physical illness, systemic failure, and allergies to tamsulosin hydrochloride sustained-release capsule drugs;

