### Interventions

2.4

Intervention group: acupuncture combined with tamsulosin hydrochloride sustained-release capsules. The acupuncture points will be selected as *Shenshu*, *Zhongliao,* and *Sanyinjiao*. The patient will be placed in the supine position. After routine disinfection of the local skin, a straight puncture of 25 to 40 mm will be performed, and twisting and replenishing and reducing methods were performed. The needle will be left for 30 minutes after getting gas, 3 times a week. The course of treatment was 4 weeks.

Control group: Tamsulosin hydrochloride sustained-release capsules (Brand name: Harlot, manufactured by Astellas Pharmaceutical Co., Ltd., specifications: 0.2 mg × 10 capsules), 0.2 mg each time, orally before bedtime, once a night. The course of treatment was 4 weeks.

Treatment will be performed once a week for a total of 4 weeks at approximately the same time in the afternoon. No restrictions will be imposed on the standard treatments for pain or any other disease during this study. If the patient is discharged according to the clinical evolution or is deceased, he/she will be excluded from this study. Further, occurrence of a serious adverse event or withdrawal of consent will result to study exclusion. During the treatment, all patients should not take other drugs that have a therapeutic effect on the disease.

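### The pre-study washout and the in-trial rule cover drugs only, so men who have just had acupuncture can enter either arm of a trial that tests acupuncture

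*Protocol article*

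**What the plan says.** Setting and participants (2.2) gives numbered eligibility lists. Inclusion criterion 4 deals with earlier treatment: "Patients who have been treated before the consultation can be included in the study after at least 2 weeks of drug withdrawal". Criterion 2 admits "Those whose disease course exceeds 3 months". The four exclusion items cover pelvic surgery, urogenital abnormality or infection, named prostate and urethral diseases, and a last item: "Patients with severe physical illness, systemic failure, and allergies to tamsulosin hydrochloride sustained-release capsule drugs". None refers to acupuncture or to any other non-drug treatment.

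Interventions (2.4) defines the arms as "Intervention group: acupuncture combined with tamsulosin hydrochloride sustained-release capsules" and "Control group: Tamsulosin hydrochloride sustained-release capsules". On other treatment during the trial it says "During the treatment, all patients should not take other drugs that have a therapeutic effect on the disease". The same paragraph also says that standard treatments for pain or other diseases are not restricted.

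The Introduction says that "acupuncture has been widely used in clinical practice". The abstract states "Simple randomization to conventional drug treatment with a 1:1 allocation ratio will be used" and mentions no stratification.

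**The concern.** By setting a washout, the article accepts that earlier treatment can contaminate entry. It applies the washout to drugs, which both arms receive as background, and not to acupuncture, which only one arm is meant to receive. Both the entry rule and the in-trial rule are silent on acupuncture received outside the trial.

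Two things are at stake. The first is the pre-treatment score. If recent needling has lowered it, it no longer describes the disease before acupuncture, and the secondary outcome divides by it. The second is the contrast between arms. Controls may carry some of the tested treatment, and the intervention arm may include men for whom acupuncture has recently worked or recently failed.

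**Working it through.** No figure in the article bears on this point, so the check is a reading of the rules followed by algebra on the outcome definition.

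**Step 1. Apply the printed rules to one patient.** Take a man aged 20 to 50 who meets the diagnostic criteria, has had symptoms for more than 3 months, has taken no drug for 2 weeks, had acupuncture yesterday, and has signed consent.

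| Rule | Does it stop or delay him? |
|---|---|
| Inclusion 1, 2, 3 and 5 | No |
| Inclusion 4 (drug withdrawal) | No: he is off drugs |
| Exclusions 1 to 4 | No: none concerns acupuncture |
| In-trial rule in 2.4 | No: it concerns other drugs |

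He is eligible, can be allocated to either arm, and if he is a control no printed rule stops him continuing acupuncture elsewhere.

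**Step 2. See what carry-over does to the outcomes.** Secondary outcomes (2.7) defines response as (pre-treatment score − post-treatment score) ÷ pre-treatment score, cut at 30%, 60% and 90%. The symbols below are assumptions, because the article gives no values:

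- S: pre-treatment score without recent acupuncture
- d: improvement by week 4 on the drug
- t: improvement by week 4 from trial acupuncture
- c: carry-over already present at baseline in a recently needled man

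All are positive, with c < t and d + t < S.

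| Case | Control, week 4 | Acupuncture, week 4 | Difference in score | Difference in proportional reduction |
|---|---|---|---|---|
| No carry-over | S − d | S − d − t | t | t/S |
| A. Persists and adds | S − c − d | S − c − d − t | t | t/(S − c), larger than t/S |
| B. Persists, acupuncture benefit capped at t | S − c − d | S − d − t | t − c | (t − c)/(S − c), smaller than t/S because S > t |
| C. Worn off by week 4 | S − d | S − d − t | t | t/(S − c), larger than t/S |

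In A to C the pre-treatment score is S − c. If a fraction q of men are recently needled, the trial-wide difference is (1 − q) × the first row + q × the row that applies.

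**Step 3. Read the result.**

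- On the week-4 score, additive carry-over cancels between randomised arms (A), and so does carry-over that has worn off (C). Only the ceiling case (B) shrinks the difference.
- On proportional reduction, the difference shrinks under B and widens under A and C.
- The control arm's own reduction rises to d/(S − c) under A and B. Under C it falls to (d − c)/(S − c), which is below d/S because d < S.
- Enrolling recent failures or responders changes t itself, downwards or upwards.

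The baseline is altered in every carry-over case. The direction of the effect on the contrast depends on facts that the article does not report.

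**The case against.** The strongest reply is that criterion 4 is coherent as a drug washout, that a journal article condenses a fuller protocol, and that the abstract calls the trial pragmatic, which suits broad entry. Randomisation also places recently needled men in both arms.

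The point about randomisation stands: no systematic imbalance is to be expected, although simple randomisation without stated stratification leaves chance imbalance possible. The point about condensation does not dispose of the matter, because the article prints its washout rule and a numbered list, and the gap lies in the wording of a stated rule. The pragmatic label carries limited weight, because the design already imposes a washout, and Study design and settings (2.1) describes a placebo-controlled trial of efficacy.

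Three stronger readings should be resisted:

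- **A fixed dilution.** A reader might infer that the planned contrast of 0.80 − 0.65 = 0.15 in Sample size (2.8.1) shrinks by a calculable amount. The article gives neither the share of recently needled men nor the persistence of the effect. Cases A and C show that dilution is not even assured. The primary outcome is also the NIH-CPSI score, not that rate.
- **Likely exposure.** The Introduction describes acupuncture use in general, not recent use for this condition, and recruitment is from urology and andrology departments. The text supports that such men can enter, not that many will.
- **No baseline record.** Table 1 is not shown, so treatment history cannot be called missing.

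**Conclusion.** The gap is real and is visible in the printed rules: the tested treatment is outside both the washout and the in-trial restriction. The consequence is a pre-treatment score that may reflect recent acupuncture, and a contrast that may be blurred if benefit has a ceiling or if recent failures or responders are enrolled. Size and direction cannot be stated. The conclusion assumes only that some recently treated men may present and that an acupuncture effect may outlast the last session. It does not assert a biased comparison or a known loss of power. Severity is minor: it is a cheap improvement.

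**What to change.** Extend inclusion criterion 4 so that the treatment-free period before entry also covers acupuncture and related needling treatments, with the interval set by the sponsor. Align the concomitant-treatment wording in Interventions with it, so that acupuncture outside the trial is addressed, and reconcile the two statements there on unrestricted standard treatment and prohibited other drugs. If it is not already recorded, note prior acupuncture at baseline (ever or never, and time since the last session).

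The cost is a phrase in each of two rules and at most one baseline field. Some recently treated men will enter later or not at all. Trial status (4) says recruitment had not begun at submission; made before recruitment begins, the change affects no enrolled patient.

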### Randomization, allocation concealment, and blinding

2.3

The web-based online randomization system to be used in this trial was provided by an independent academic data management center at Dongzhimen Hospital Affiliated to Beijing University of Chinese Medicine. The attending Physician will identify eligible patients according to the inclusion and exclusion criteria. Informed consent will be taken by the attending physician, and participants will be referred to a research coordinator who will randomly assign them to the intervention or control arm. The randomization list is kept by the biostatistician and research coordinator until the end of the study to ensure allocation concealment; therefore, the data analysts will be kept blinded to the allocation. The participants will be instructed not to disclose the allocation to the attending physician.

### Interventions

2.4

Intervention group: acupuncture combined with tamsulosin hydrochloride sustained-release capsules. The acupuncture points will be selected as *Shenshu*, *Zhongliao,* and *Sanyinjiao*. The patient will be placed in the supine position. After routine disinfection of the local skin, a straight puncture of 25 to 40 mm will be performed, and twisting and replenishing and reducing methods were performed. The needle will be left for 30 minutes after getting gas, 3 times a week. The course of treatment was 4 weeks.

Control group: Tamsulosin hydrochloride sustained-release capsules (Brand name: Harlot, manufactured by Astellas Pharmaceutical Co., Ltd., specifications: 0.2 mg × 10 capsules), 0.2 mg each time, orally before bedtime, once a night. The course of treatment was 4 weeks.

Treatment will be performed once a week for a total of 4 weeks at approximately the same time in the afternoon. No restrictions will be imposed on the standard treatments for pain or any other disease during this study. If the patient is discharged according to the clinical evolution or is deceased, he/she will be excluded from this study. Further, occurrence of a serious adverse event or withdrawal of consent will result to study exclusion. During the treatment, all patients should not take other drugs that have a therapeutic effect on the disease.

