#### Analysis set

2.8.2

The Full Analysis Set will be used for all primary analysis. Per Protocol Set analysis will be performed for evaluating the sensitivity of results.

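### The visible text gives the number of acupuncture sessions in three incompatible ways: 10, 12 or 4

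*Protocol article*

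**What the plan says.** Three statements in the protocol article describe how much acupuncture the intervention arm receives.

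- **Abstract, Methods/design:** "Ten 30-minute acupuncture sessions will be provided to patients assigned to the Intervention group".
- **Section 2.4 Interventions, intervention-group paragraph:** "The needle will be left for 30 minutes after getting gas, 3 times a week". The same paragraph gives the length: "The course of treatment was 4 weeks".
- **Section 2.4 Interventions, closing paragraph, after both arms have been described:** "Treatment will be performed once a week for a total of 4 weeks at approximately the same time in the afternoon".

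The only other study treatment described is tamsulosin, which the control-group paragraph gives as "0.2 mg each time, orally before bedtime, once a night".

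Section 2.8.2 (Analysis set) bases the primary analyses on the Full Analysis Set and adds: "Per Protocol Set analysis will be performed for evaluating the sensitivity of results".

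All of this is current text, not a record of superseded wording.

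**The concern.** The session count is a defining feature of the experimental arm. Each of the three statements reads as an instruction, and each leads to a different total. Two of them stand in the same section.

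Two things are at stake. First, a practitioner who follows any one of the sentences complies with the text, so different patients could receive different regimens with no recorded deviation. A reader of the results could not tell from this text which regimen had been planned. Second, any later rule for membership of the Per Protocol Set has to refer to a planned course, and the visible text offers three.

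**Working it through.** **Inputs**

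- Abstract: 10 sessions of 30 minutes.
- Section 2.4, intervention paragraph: 3 sessions a week, 30 minutes each, for 4 weeks.
- Section 2.4, closing paragraph: 1 treatment a week for 4 weeks. No session length is given there, so the 30 minutes stated elsewhere is assumed.

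**Formula:** sessions = frequency per week × weeks; needling time = sessions × 30 minutes.

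**Can the abstract's figure of 10 be reproduced?** No.

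- From the intervention paragraph: 3 × 4 = 12.
- From the closing paragraph: 1 × 4 = 4.
- Working backwards: 10 ÷ 4 weeks = 2.5 sessions a week, which matches neither stated frequency.

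| Source | Sessions | Needling time | 4 sessions attended, as a share of the course |
|---|---|---|---|
| Abstract | 10 | 10 × 30 = 300 min | 4/10 = 40% |
| 2.4, intervention paragraph | 12 | 12 × 30 = 360 min | 4/12 = 33% |
| 2.4, closing paragraph | 4 | 4 × 30 = 120 min | 4/4 = 100% |

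The largest total is 12/4 = 3 times the smallest.

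**Could the weekly sentence mean something other than acupuncture?**

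- It cannot mean the capsule, which is taken every night at bedtime and not weekly in the afternoon.
- It could be meant as a visit schedule, but it speaks of treatment being performed, and acupuncture is the only other treatment described.
- If it is set aside altogether, the abstract's 10 still conflicts with the 12 from section 2.4. The gap is then 2 sessions, or 60 minutes, and 10/12 = 83% of the longer course.

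The contradiction therefore does not depend on how the weekly sentence is read. Only its size does.

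**The case against.** Five points can fairly be made on the other side.

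**Table 1 is not shown.** Its caption says that it carries the treatment schedule, and it may fix one. A reader might infer from the three statements that the intervention is undefined. The documents do not support that, because the table is unseen. What they support is that the visible text contradicts itself. A clear table would agree with at most one of the three totals, so the conflict would remain.

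**The statements do not carry equal weight.** The three-times-weekly figure is the only one in the labelled intervention-group paragraph, where it is tied to the needling procedure. The abstract is a summary. The weekly sentence has an unspecified subject and may be misplaced. This is a reasonable observation, and the threefold range does rest on that weakest sentence. It does not remove the 10 against 12, and it does not settle which schedule is intended.

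**Adherence rules belong elsewhere.** A reader might infer that the article is at fault for not defining Per Protocol adherence. It is not. Such a threshold is commonly left to the SAP or the full protocol, neither of which is shown, and the primary analyses use the Full Analysis Set in any case. The narrower point stands: the text supplies no single planned course for such a rule to use.

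**Mixed exposure is a possibility, not a fact.** A reader might infer that sites will deliver different treatments and that the effect estimate will average unknown exposures. The number of sites is itself unclear: section 2.1 calls the trial multi-center and section 2.9 mentions collaborating hospitals, while section 2.2 recruits from one hospital. Section 2.9 also plans recurrent training and monthly central monitoring, and delivered sessions could be recorded on the case report forms. Training and monitoring cannot resolve a contradictory text, but they may lead everyone to apply one reading of it.

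**An article condenses the full protocol.** That would excuse omitted detail. It does not excuse stated figures that conflict.

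**Conclusion.** The point holds. The visible text gives the acupuncture course as 10, 12 or 4 sessions, and no visible statement reconciles them. The range is threefold if all three statements are counted, and 10 against 12 if the weekly sentence is discounted. The needling times of 300, 360 and 120 minutes assume that the weekly treatments also last 30 minutes; the session counts need no assumption beyond the stated frequencies and the 4-week course.

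The text must be corrected because the session count defines the arm being tested, and literal compliance can produce different regimens. The conclusion does not rest on a missing adherence threshold or on a prediction about how sites will behave.

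**What to change.** Before recruitment, reconcile the abstract and both statements in section 2.4, and check Table 1 against them, so that one session count, one weekly frequency and one duration appear throughout. Remove the statements that conflict with it. If the weekly afternoon sentence was meant for something other than acupuncture, say what. Which schedule is right is a clinical decision for the sponsor, and no view is taken on it here. Any later definition of the Per Protocol Set, wherever it is written, can then refer to that single course.

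The cost is a text correction. Section 4 (Trial status) says that recruitment had not begun when the article was submitted, so at that point no patient was affected. Once patients have been treated under differing readings, their exposure cannot be made uniform afterwards.

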### Quality control and trial management

2.9

The management structure will comprise the principal investigator (PI), a trial management group, and a data monitoring committee. The trial management group will be responsible for conducting the trial and will meet monthly to discuss the trial progress. The PI will visit each collaborative hospital for face-to-face meetings and to share information to promote patient recruitment. The data monitoring committee will review safety and efficacy data. All data will be monitored every month through a central monitoring method. Additional monitoring may be performed at the discretion of the monitoring manager. The data monitoring committee have met once prior to the start of patient recruitment. At least twice per year, participating investigators, research assistants, and research nurses will be required to attend a training workshop on clinical research to ensure strict adherence to the study protocol and familiarity with the trial administration process. The data collected in this trial will comprise information recorded in case report forms and questionnaires. Data quality will be checked regularly by research assistants and overseen by monitors; all modifications will be marked on case report forms and data managers will recheck the data before they are officially logged. The database will be locked after all data have been cleaned. If participants withdraw from the trial during the study period, the reasons will be documented and the dropout rate will be statistically analyzed.

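### As worded, excluding randomised patients after discharge, death, a serious adverse event or withdrawal of consent conflicts with the Full Analysis Set primary analysis and the safety aim

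*Protocol article*

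**What the plan says.** Section 2.4 (Interventions) has two consecutive sentences on patients who leave. The first reads "If the patient is discharged according to the clinical evolution or is deceased, he/she will be excluded from this study". The second adds that "occurrence of a serious adverse event or withdrawal of consent will result to study exclusion".

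These are not entry criteria, which are listed separately in section 2.2. Under section 2.3, once consent is given, "participants will be referred to a research coordinator who will randomly assign them to the intervention or control arm". An event during the four-week course therefore comes after randomisation.

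On analysis, section 2.8.2 says "The Full Analysis Set will be used for all primary analysis" and "Per Protocol Set analysis will be performed for evaluating the sensitivity of results". It does not define either set. On aims, section 2.1 says the trial is to "evaluate the efficacy and safety of acupuncture for patients with CP/CPPS". Section 2.9 says "The data monitoring committee will review safety and efficacy data". It also says that reasons for withdrawal are recorded and that the dropout rate is analysed.

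**The concern.** A Full Analysis Set is meant to keep patients as randomised, as far as possible. The rule in section 2.4 takes randomised patients out of the study because of what happens to them afterwards. Each trigger can depend on the treatment received or on how the patient is doing:

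- Discharge is tied to the clinical course.
- A serious adverse event may be caused by treatment.
- Consent may be withdrawn because of lack of benefit or because of burden, and only one arm is needled.

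If the triggers act differently in the two arms, the patients left are no longer the groups that randomisation formed.

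Two things are at stake. The first is the week-4 NIH-CPSI comparison. If these patients are out of the study altogether, they are missing from both the Full Analysis Set and the Per Protocol Set, and comparing the two sets could not reveal the selection. The second is safety. In a trial with a stated safety aim, the patients named for exclusion include exactly those with a serious adverse event or death.

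**Working it through.** **Reading the sections together**

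1. Section 2.3: allocation follows consent and precedes treatment.
2. Section 2.4: four events, which can all occur during treatment, lead to exclusion from the study.
3. Section 2.8.2: the primary analysis uses the Full Analysis Set. No sentence says that patients excluded under section 2.4 stay in it.
4. Section 2.1: safety is an aim. No sentence says that excluded patients are counted in safety results by arm.
5. Section 2.9: withdrawal reasons, the dropout rate and committee review are covered. None of these puts a patient back into the efficacy or safety comparison between arms.

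Steps 2 and 3 conflict as worded, and so do steps 2 and 4. Step 5 does not resolve either conflict.

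**Possible size for the week-4 score**

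The plan gives no figure on this point, so there is none to reproduce. Let p_A and p_C be the shares excluded in the acupuncture and control arms. Let g be the difference in mean outcome between excluded and retained patients, in SD, taken as equal in both arms. Dropping a share p shifts an arm's mean by p × g, so

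bias in the difference = (p_A − p_C) × g.

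The standard error of the difference in SD units, at the plan's 75 per arm after losses (section 2.8.1), is √(2/75) = 0.163. The 75 is used here only as the planned number; how it was derived is a separate question. The values of p_A, p_C and g are assumptions: p_A 5-10%, p_C 0-5%, g 0.5-1 SD.

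| p_A vs p_C | Difference | Bias at g = 0.5 to 1 | In standard errors |
|---|---|---|---|
| 5% vs 5% | 0 | 0 | 0 |
| 5% vs 0%, or 10% vs 5% | 0.05 | 0.025 to 0.05 SD | 0.15 to 0.31 |
| 10% vs 0% | 0.10 | 0.05 to 0.10 SD | 0.31 to 0.61 |

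The range is therefore 0 to 0.10 SD, or 0 to 0.6 standard errors. The sign depends on whether the excluded patients do worse or better than those kept, and on which arm loses more.

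**Illustration on the effective-rate scale of section 2.8.1**

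Assume a true rate of 0.65 in both arms and 83 per arm, so 0.65 × 83 = 53.95 expected responders. Exclude k patients from one arm only.

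| k | All k non-responders: 53.95/(83 − k) | All k responders: (53.95 − k)/(83 − k) |
|---|---|---|
| 1 | 0.658 (+0.8 points) | 0.646 (−0.4) |
| 2 | 0.666 (+1.6) | 0.641 (−0.9) |
| 4 | 0.683 (+3.3) | 0.632 (−1.8) |
| 8 | 0.719 (+6.9) | 0.613 (−3.7) |

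The planned difference is 0.80 − 0.65 = 15 points. The row k = 8 is extreme: it spends one arm's whole loss allowance on one kind of patient, with no such exclusions in the other arm.

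**Safety**

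No assumption about rates is needed. If exclusion from the study extends to the safety tables, the serious-event count in the tables is zero in both arms by construction. If it does not extend that far, nothing is lost. The article does not say which applies.

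**The case against.** The strongest reply is that section 2.4 describes treatment and speaks of exclusion from the study, not from the analysis. It may be a discontinuation rule in loose wording. The Full Analysis Set is not defined, and an article may leave that definition to the full protocol or the analysis plan. This stands in part: loss from the analysis is the plain reading, not an explicit statement. But the point concerns a rule that the article does state, and if only discontinuation was meant, the sentences still need the same clarification.

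The second reply is that few such events are likely in four weeks, in men aged 20 to 50 and with severe physical illness ruled out at entry. For efficacy this stands. The upper end of the range above gives one arm the plan's entire 10% loss allowance for these events alone, which is probably too high.

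A reader might also infer more than the documents support:

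- *That the primary set becomes a completers-only set.* It does not. Only patients with the named events leave; non-adherent patients, or those lost for other reasons, are not touched by section 2.4.
- *That serious adverse events vanish from the trial.* An event has to be recorded before it can trigger exclusion, and section 2.9 provides for committee review of safety data. What is not secured is reporting by randomised arm.
- *That the bias favours acupuncture.* The phrase on discharge is undefined and may describe patients who improved. Losing improved acupuncture patients would work against acupuncture.
- *That open treatment makes the bias certain.* Section 2.1 calls the trial single-blind and placebo-controlled, although section 2.4 describes no sham. That is a separate inconsistency, and this point does not depend on it.

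**Conclusion.** The concern holds as a conflict of wording with consequences for the analysis. Section 2.4, read plainly, removes randomised patients for events that can depend on treatment and outcome. Section 2.8.2 and the safety aim in section 2.1 need those patients, and nothing in the article restores them. This is a stated rule, not a detail left to another document.

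The effect on the efficacy estimate is unknown in sign and probably small: 0 to 0.10 SD, or up to about 0.6 standard errors, under assumed exclusion shares and outcome differences that the documents do not supply. The safety concern does not rest on those assumptions, but it does depend on the exclusion reaching the safety tables, which the article leaves open. The conclusion itself depends on none of the figures.

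**What to change.** Reconcile sections 2.4, 2.8.2 and 2.9 so that three things are kept apart: stopping study treatment, leaving follow-up, and being left out of an analysis. Any clinical rule on stopping treatment stays as the investigators set it; no change to it is proposed here. Add to the analysis-set section:

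> Discharge, death, a serious adverse event or stopping study treatment does not by itself remove a randomised patient from the Full Analysis Set or from safety reporting. NIH-CPSI is still collected at week 4 from surviving patients who have not withdrawn consent to data collection; data collected before withdrawal are kept where consent allows; and all serious adverse events and deaths are reported by randomised arm. Only the Per Protocol Set may omit these patients.

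The cost is protocol wording and a few extra week-4 questionnaires. Section 4 says recruitment had not begun at submission. The change is best made before it does, because week-4 scores not collected from excluded patients cannot be recovered later.
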